[figure not shown]

## **1.1 List of Changes**

The purpose of this amendment is to implement several format and administrative changes.

An itemized list of all changes made to the protocol under this amendment is included in Appendix.

[figure not shown]

### **3.0 List of Abbreviations**

|        |                                                                    |
|--------|--------------------------------------------------------------------|
| AE     | Adverse Event                                                      |
| eCRF   | electronic Case Report Form                                        |
| EDC    | Electronic Data Capture                                            |
| ENT    | Ear, Nose and Throat                                               |
| ICD-10 | International Classification of Diseases 10 th Revision |
| IEC    | Independent Ethics Committee                                       |
| MedDRA | Medical Dictionary for Regulatory Activities                       |
| SAE    | Serious Adverse Event                                              |

[figure not shown]

## 4.0 Introduction

Vertigo is one of the most frequent symptoms in medical practice and may be revealed in more than 80 diseases. Vertigo can be found in approximately 5% of subjects within general practitioners' practice [1] and 10% within otolaryngologist patient population [2]. According to Yardley L. during an interview of 20 thousand men, aged between 18 up to 64 it was found that more than 20% of respondents suffered from vertigo within a month, 30% of them had vertigo within 5 years [3]. In 1000 respondents older 60 years, 30% of them reported that they have had vertigo have had vertigo lifelong [4]. Approximately every third patient who visit otolaryngologist suffer from different types of vertigo [5].

Vertigo, commonly referred as illusion of movement and spatial orientation, occurs due to imbalances of signals to the vestibular apparatus [6]. There are two types of vertigo: vestibular and non-vestibular vertigo. Vestibular vertigo can be caused by lesions of the central system (the vestibular nuclei of the brainstem, vestibular and vestibular communications centers of the brain) or peripheral parts (the vestibular nerve and labyrinth) of the vestibular system. Vestibular vertigo is a common problem affecting more than 5% of adults every year [6; 7]. Various factors like female sex, age, lower educational level, and other comorbid conditions, including tinnitus, depression, several cardiovascular diseases (hypertension dyslipidemia), other risk factors, are also observed to be associated with vestibular vertigo [21].

Vestibular vertigo may be classified by the level of affecting of vestibular analyzer. (central or peripheral part of vestibular system). Vestibular vertigo is connected with irritation of certain locations of vestibular analyzer and depending on the dysfunction location can be either peripheral or central [14]. If vertigo arises from the balance centers of the brain, it is usually milder, and has accompanying neurologic deficits, such as slurred speech, double vision or pathologic nystagmus [7; 11; 12, 13]. Brain pathology can cause a sensation of disequilibrium which is an off-balance sensation.

[figure not shown]

A number of conditions that involve the central nervous system may lead to vertigo including: migraine headaches, lateral medullary syndrome, multiple sclerosis [8; 9]. Horizontal optokinetic nystagmus is a symptom which can accompany vertigo.

Peripheral vestibular vertigo is characterized by episodic or persistent occurrence and objective feeling of swaying [10]. Meniere's disease is often responsible for episodes of vertigo that heighten in severity over a period of minutes, but last for several hours with a gradual improvement during another period of several hours. Vestibular neuronitis and episodes of labyrinthitis typically present with fairly abrupt onset vertigo (over a period of hours) with resolution of the acute phase over the next several days. Traumatic injuries or vascular infarction of the labyrinth cause a sudden onset of symptoms with a slow recovery from the acute phase over a period of days to weeks, often with residual effects over a period of several months [22].

Medical management of vestibular vertigo may range from home care therapy to other medical interventional options available based on the type of disease condition the patient is suffering from. Specific types of vestibular vertigo may require additional treatment and referral.

### **Betahistine**

Betahistine was first registered in Canada in 1968 and, to date, is approved in >115 countries for Meniere's disease and the symptomatic treatment of vertigo. The increased amounts of histamine released from histaminergic nerve endings can stimulate H1 receptors, thus augmenting the direct agonistic effects of betahistine on these receptors. This would additionally explain the potent vasodilatory effects of betahistine in the inner ear, which are well documented [15]. The reduction in the number of attacks is achieved by betahistine treatment via increase in blood flow to the inner ear. This reduces the increased endolymphatic pressure in the inner ear by achieving a balance between production and re-absorption of endolymph [16]. In addition, betahistine strongly demonstrates facilitation of vestibular compensation through various animal models by a clear action on the histaminergic system; wherein it increases the histamine turnover and

[figure not shown]

release by blocking pre-synaptic histamine H3 auto receptors (both in vestibular and tuberomammillary nuclei) [15].

In clinical practice in Russia and Ukraine, betahistine dihydrochloride is administered at a dosage of 24-48 mg per day orally either as monotherapy or as adjunctive therapy when current anti-vertigo therapy is not sufficient or not tolerated.

## **5.0 Rationale**

The purposes of this international post-marketing observational program is to investigate effectiveness of betahistine dihydrochloride (Betaserc®) tablets and assess the course of vestibular vertigo in post-treatment period in population of Russia and Ukraine outpatients suffering from vestibular vertigo in pragmatic clinical settings. The special goal of this study is to evaluate the use of Betahistine dihydrochloride in the maximal recommended daily dose of 48 mg in accordance with the locally approved label.

As it is well known that 2 – 3 months betahistine dihydrochloride therapy may accelerate and facilitate vestibular compensation in patients with vestibular dysfunction [23, 24] this study is also intended to assess the course of vestibular vertigo after Betaserc® discontinuation in descriptive manner. Two month length of follow-up period was selected because it is considered as an adequate time-point of symptom back for the majority of underlying neurological and otolaryngological conditions (unpublished data from Russian and Ukrainian academic neurologists and otorhinolaryngologists communications).

Exploratory analyses of results from both participating countries may be expected to provide insights about the subjective circumstances of vestibular vertigo patients in a wider than usual range of gender, underlying ICD-10 diagnosis, national and cultural situations.

[figure not shown]

## **6.0 Study Objectives**

### **6.1 Primary Objective**

1. To assess the effectiveness of betahistine dihydrochloride tablets 48mg/day therapy in routine outpatient clinical settings in population of subjects with vestibular vertigo.

### **6.2 Secondary Objectives**

1. To assess the overall clinical response and clinical response as improvement of vertigo associated symptoms over treatment period.
2. To assess the course of vestibular vertigo over the 2-month post-treatment follow-up period.
3. To describe underlying diagnosis according to ICD-10 that account for vestibular vertigo.

### **6.3 Primary Endpoint**

1. Number and proportion of patients with clinical response at the end of observational treatment period that is determined based on the Scale for Vestibular Vertigo Severity Level and Clinical Response Evaluation (SVVSLCRE) (Figure 1 and Table 1) in the total program population.

The patients will evaluate vestibular vertigo severity at baseline and end of observational treatment period based on the SVVSLCRE.

[figure not shown]

**Figure 1. Scale for Vestibular Vertigo Severity Level and Clinical Response Evaluation (SVVSLCRE).**

| Severity levels:   |   | Level I.
Absent or very mild vestibular vertigo
0 – 2   |   | Level II.
Mild vestibular vertigo
>2 – 4                                    |   | Level III.
Moderate vestibular vertigo
>4 – 6                                  |   | Level IV.
Severe vestibular vertigo
>6 – 8          |   | Level V.
Very severe vestibular vertigo
>8 – 10    |  |
|--------------------|---|---------------------------------------------------------------|---|-----------------------------------------------------------------------------------|---|--------------------------------------------------------------------------------------|---|-----------------------------------------------------------|---|----------------------------------------------------------|--|
|                    |   | Disturbances can be easy ignored. activities is not disrupted |   | Disturbances can be ignored with some efforts, activities can be slightly limited |   | Disturbances can be ignored with great efforts, activities can be moderately limited |   | Disturbances cannot be ignored, most activities disrupted |   | Disturbances cannot be ignored, all activities disrupted |  |
| 0                  | 1 | 2                                                             | 3 | 4                                                                                 | 5 | 6                                                                                    | 7 | 8                                                         | 9 | 10                                                       |  |
| Absent of symptoms |   | Very severe symptoms                                          |   |                                                                                   |   |                                                                                      |   |                                                           |   |                                                          |  |

[figure not shown]

**Table 1. Clinical responses define as a following:**

| Change of patient's clinical conditions of vestibular vertigo | Shift direction based on the SVVSLCRE from Baseline to end of observational treatment period |
|----------------------------------------------------------------------|-----------------------------------------------------------------------------------------------------|
| Worsening                                                            | All other shifts                                                                                    |
| No change                                                            | V to V; IV to IV; III to III; I to I                                                                |
| Moderate                                                             | V to IV; IV to III; III to II; II to I                                                              |
| Good                                                                 | V to III; IV to II; III to I                                                                        |
| Very good                                                            | V to II; IV to I                                                                                    |
| Excellent                                                            | V to I                                                                                              |

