### **Sample size considerations**

Based on evaluation of literature data that was published by Gananca et al. in *Acta Oto-Laryngologica*, 2009 [17], proportion of patients with Meniere's Disease achieved control of vertigo (clinical conditions levels 4 and 3) after 12 weeks of treatment with betahistine dihydrochloride tablets constituted 88%. Benecke et al. [18] found that overall efficacy of betahistine in routine clinical practice over 3 months therapy was excellent by 36.6% of 1753 patients with recorded data (n = 641) and good by 49.6% of patients (n = 870), total 86.2 %. The investigators' impression of the treatment was excellent for 38.6% of patients (n = 675 of 1747) and good for 50.5% of patients (n = 883), total 89.1%.

For this program, it is assumed that at least 80% of the total study sample will achieve clinical response after 60 days of therapy with betahistine dihydrochloride tablets. When the sample size without a consideration of dropout is 246, a normal approximation two-sided 95% confidence interval for a single proportion using normal distribution will extend 5.0% (i.e. half width of the 95% confidence interval) from the observed proportion for an expected proportion of 80% [19; 20]. Considering an approximate dropout rate about 20%, total study population (received at least one dose of betahistine dihydrochloride (Betaseron®) tablets and have at least one post-baseline assessment) will constitute 308 patients.

Overall, the best consideration for total number of enrolled patients with vestibular vertigo in the program has to amount 310.

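### Table 1 classes an unchanged Level II patient as Worsening, and the protocol does not say which of its rows count as the primary clinical response

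*Protocol*

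**What the plan says.** Section 6.3 gives one primary endpoint: "Number and proportion of patients with clinical response at the end of observational treatment period", determined from the severity scale in Figure 1 and the shift categories in Table 1. Figure 1 has five severity levels, I to V.

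Table 1 is headed "Clinical responses define as a following" and has six rows: Worsening, No change, Moderate, Good, Very good and Excellent. Three rows matter here:

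- No change: "V to V; IV to IV; III to III; I to I"
- Worsening: "All other shifts"
- Moderate: "V to IV; IV to III; III to II; II to I"

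Section 11.0, Analysis of Primary Endpoint, plans the proportion with clinical response and a normal-approximation 95% interval. Under Sample size considerations, "it is assumed that at least 80% of the total study sample will achieve clinical response after 60 days of therapy". Neither place says which rows of Table 1 are responses.

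**The concern.** There are two defects, both in the wording of the primary endpoint's definition.

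First, the No change row lists four of the five possible unchanged shifts. Because Worsening is a catch-all, the missing one is not left unclassified: it is assigned to Worsening. Such patients can be enrolled, since Section 7.1.1 sets no minimum severity and Table 1 itself provides for improvement from Level II. A program written literally from the table would reproduce the error.

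Second, the table heading covers all six rows, and nothing in Sections 6.3 or 11.0 marks where response begins. The primary estimate, and the event that the 80% assumption describes, both depend on that cut.

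**Working it through.** **Planning figure.** Inputs from Section 11.0, Sample size considerations: p = 0.80, half-width h = 0.05, two-sided 95% interval, 20% dropout.

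- n = 1.96² × 0.80 × 0.20 / 0.05² = 245.9, rounded up to 246.
- 246 / (1 − 0.20) = 307.5, rounded up to 308. The protocol then rounds to 310.

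All the stated figures reproduce, and this point does not challenge them.

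**Enumeration of Table 1.** Five baseline levels by five end levels give 25 shifts.

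| Row | As written | With II to II moved |
|---|---|---|
| Worsening | 11 | 10 |
| No change | 4 | 5 |
| Moderate | 4 | 4 |
| Good | 3 | 3 |
| Very good | 2 | 2 |
| Excellent | 1 | 1 |
| Total | 25 | 25 |

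Fourteen shifts are named and 11 fall to the catch-all. Ten of those 11 are moves to a higher level. The eleventh is II to II, the only misplaced cell.

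**Size of the misclassification.** The protocol gives no baseline distribution, so both inputs are assumptions: 10–30% of patients start at Level II, and 20–40% of them end there.

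- Low: 0.10 × 0.20 = 2%; 0.02 × 246 = 4.9, about 5 patients.
- High: 0.30 × 0.40 = 12%; 0.12 × 246 = 29.5, about 30 patients.

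**Effect of the responder cut.**

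| Rows counted as response | Shifts counted | Baseline levels that can respond |
|---|---|---|
| Moderate or better | 10 | II to V |
| Good or better | 6 | III to V |
| No change or better | 14 as written, 15 corrected | I to V |
| All rows (heading taken literally) | 25 | I to V |

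Of the first three cuts, only No change or better makes the place of II to II alter the primary proportion. A Level I entrant cannot respond under either of the first two.

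**Illustration of the gap between cuts.** Suppose 15% start at Level II, the rest at III to V, none at I. Suppose also that 20% do not improve, 35% drop one level and 45% drop two or more, with Level II patients limited to a one-level drop. Moderate or better is then 80%, by construction. Good or better is 0.85 × 45% = 38%, a gap of about 42 points. Moving the Level II share over 10–30% gives 0.90 × 45% = 40.5% to 0.70 × 45% = 31.5%, so gaps of 39.5 to 48.5 points. These follow from the invented mix and show only that the cut can matter more than the planned 5-point half-width.

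**Precision if the cut lowers the rate.** At n = 246 the half-width is 5.7 points at an assumed 70%, 6.1 at 60% and 6.25 at 50%. Holding 5 points would take 323, 369 and 385 evaluable patients.

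**The case against.** The strongest reply is that neither defect shows the primary result to be wrong. If response means improvement, a II-to-II patient is a non-responder under either label. That stands: a reader might infer from the misplaced cell that the response proportion is biased, and the documents do not support it.

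Nor is a worsening rate a named endpoint. Section 6.4, endpoint 1, tabulates scale categories at baseline as well as at the end, so these must be the severity levels, where II to II is counted correctly. Endpoints 2 and 3 are analysed by medians, quartiles and a Wilcoxon test. A worsening count would arise only from the general rule in Section 11.0 that qualitative variables are summarised by category. That also stands, and is why the effect is stated for any tabulation of Table 1 rather than for a planned result.

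On the cut, Moderate through Excellent are plainly grades of improvement, and an 80% assumption makes no sense if every row counts. Moderate or better is therefore the natural reading. It is still not stated, and two parts of the protocol weaken it. Section 6.4 also uses clinical response for a graded rating whose lowest category is poor. The literature cited for the 80% sums only upper categories: levels 4 and 3 for the 88%, and excellent plus good for the 86.2% (36.6 + 49.6) and 89.1% (38.6 + 50.5). These are other scales, so they do not settle where Moderate falls on this one.

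Finally, a reader might infer that the sponsor can choose the cut after seeing the shifts. The protocol does not show that. A statistical analysis plan is announced, there for exploratory methods, and may fix the cut. Even so, the responder definition of the sole primary endpoint belongs where that endpoint is defined.

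**Conclusion.** The concern holds in limited form. As written, Table 1 misclassifies one of 25 shifts: a stable Level II patient is called worse. On the assumed ranges above, that moves 2–12% of patients from No change to Worsening in any table of these categories. It leaves the primary proportion unchanged if response means at least one level of improvement.

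The unstated cut is the weightier part. The text favours Moderate or better without saying so, and the 80% assumption has no explicit referent. Under Good or better, all Level I and II entrants would be non-responders by construction. How far the two cuts would differ in this population cannot be known from the protocol, so the gap computed above is illustrative only.

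**What to change.** - In Table 1, add II to II to the No change row and define Worsening as any shift to a higher severity level, in place of the catch-all.
- In Sections 6.3 and 11.0, have the sponsor state which rows are the primary clinical response, before data are reviewed. Moderate or better, meaning improvement by at least one level, fits Table 1 best.
- Under Sample size considerations, confirm that the 80% refers to that cut.

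The cost is wording only. No new data are needed, and 246, 308 and 310 stand if 80% is the expected rate for the chosen cut. If the sponsor intends a stricter cut with a lower expected rate, the stated precision would need to be recalculated.

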#### **6.4 Secondary Endpoints**

1. Number and proportion of patients in each category of SVVSLCRE at baseline and end of observational treatment period in patients who completed betahistine treatment over a period less or equal 30 days and in patients who completed betahistine treatment over a period more than 30 days but less or equal 60 days.
2. Change of the patient's clinical conditions of vestibular vertigo assessed with SVVSLCRE from baseline to the end of observational treatment period in patients who completed betahistine treatment over a period less or equal 30 days and in patients who completed betahistine treatment over a period more than 30 days but less or equal 60 days.
3. Change of the patient's clinical conditions of vestibular vertigo assessed with SVVSLCRE from baseline to Visit 2 in patients who completed betahistine treatment over a period more than 30 days but less or equal 60 days.

[figure not shown]

4. Change of vestibular vertigo attacks frequency from baseline to the end of observational treatment period in patients who completed betahistine treatment over a period less or equal 30 days and in patients who completed betahistine treatment over a period more than 30 days but less or equal 60 days.
5. Change of vestibular vertigo attacks frequency from baseline to Visit 2 in patients who completed betahistine treatment over a period more than 30 days but less or equal 60 days.
6. Overall clinical response assessed by physician will be determined based on a four-point-scale, where 4 = excellent, 3 = good, 2 = fair, and 1 = poor. Proportion of patients in each category at the end of observational treatment period will be determined in patients who completed betahistine treatment over a period less or equal 30 days and in patients who completed betahistine treatment over a period more than 30 days but less or equal 60 days. Proportion of patients in each category at Visit 2 will be determined in patients who completed betahistine treatment over a period more than 30 days but less or equal 60 days.
7. Overall clinical response assessed by patient will be determined based on a four-point-scale, where 4 = excellent, 3 = good, 2 = fair, and 1 = poor. Proportion of patients in each category at the end of observational treatment period will be determined in patients who completed betahistine treatment over a period less or equal 30 days and in patients who completed betahistine treatment over a period more than 30 days but less or equal 60 days. Proportion of patients in each category at Visit 2 will be determined in patients who completed betahistine treatment over a period more than 30 days but less or equal 60 days.
8. Clinical response as improvement of vertigo associated symptoms (tinnitus, hearing loss, nausea, vomiting, faintness and headache) and evaluated by physician will be determined based on a four-point-scale, where 4 = excellent, 3 = good, 2 = fair, and 1 = poor. Proportion of patients in each category at the end of observational treatment period will be determined in patients who completed betahistine treatment over a period less or equal 30 days and in patients who completed betahistine treatment over a period more

[figure not shown]

than 30 days but less or equal 60 days. Proportion of patients in each category at Visit 2 will be determined in patients who completed betahistine treatment over a period more than 30 days but less or equal 60 days.

9. Clinical response as improvement of vertigo associated symptoms (tinnitus, hearing loss, nausea, vomiting, faintness and headache) and evaluated by patient will be determined based on a four-point-scale, where 4 = excellent, 3 = good, 2 = fair, and 1 = poor. Proportion of patients in each category at the end of observational treatment period will be determined in patients who completed betahistine treatment over a period less or equal 30 days and in patients who completed betahistine treatment over a period more than 30 days but less or equal 60 days. Proportion of patients in each category at Visit 2 will be determined in patients who completed betahistine treatment over a period more than 30 days but less or equal 60 days.

10. Change of vestibular vertigo attacks frequency from the end of observational treatment period to the end of 1st month of follow-up period in patients who completed betahistine treatment over a period less or equal 30 days and in patients who completed betahistine treatment over a period more than 30 days but less or equal 60 days.

11. Change of vestibular vertigo attacks frequency from the end of observational treatment period to the end of 2nd month of follow-up period (end of follow-up period) in patients who completed betahistine treatment over a period less or equal 30 days and in patients who completed betahistine treatment over a period more than 30 days but less or equal 60 days.

12. Specific underlying ICD-10 diagnosis account for Vestibular Vertigo. Proportion of patients in each category at Visit 1 will be determined in total study population.

[figure not shown]

